#### Hypothesis 1: Group-level behavioral effects.

To assess whether participation in the Dinosaur Child Program leads to greater improvements in children’s emotional, social, behavioral and cognitive functioning, LCS models will be estimated in Mplus for each primary outcome domain: child externalizing behavior, social competence, emotional understanding, and cognitive functioning. Outcomes will be analyzed separately for parent-reported, teacher-reported, and child-assessed measures. LCS models estimate change over time using latent difference scores, thereby distinguishing true change from measurement error. Intervention condition will be tested as a predictor of pre-to-post change examine differential improvements between the intervention and control group. Each latent change score model will estimate the average change over time, interindividual variability in change, and the effect of group assignment on these change scores. Bonferroni-adjusted significance thresholds will be applied to control for multiple comparisons across outcome domains.

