### Study aim and research questions

The overarching aim of this study is to evaluate the effectiveness of the Dinosaur Child Program in reducing externalizing behavior and improving emotional and social functioning in children aged 4–8. Furthermore, the study aims to explore individual variability in intervention response and real-time parent–child dynamics using the daily diary methodology.

Specifically, the following research questions and hypotheses are addressed:

1. **Does participation in the Dinosaur Child Program lead to greater improvements in children’s emotional, social, and cognitive functioning, and reductions in externalizing behavior compared to a waitlist control group?**

*H1*: We hypothesize that children in the intervention group will show significantly more improvement in teacher- and parent-reported social, emotional, and cognitive/linguistic competencies, and significantly greater reductions in externalizing behavior than children in the control group.

2. **Does the intervention lead to reduced emotional variability and fewer daily behavior problems, as captured through daily diary methodology?**

*H2*: We hypothesize that children in the intervention group will exhibit fewer and less intense fluctuations in negative affect (controlled for mean level changes) and fewer moments of defiance, tantrums, or other behavior problems across the day, compared to the control group.

3. **Does the intervention alter day-to-day parent–child dynamics by reducing children’s experience of negative affect and promoting shared positive affect in interaction with their parents?**

*H3*: We hypothesize that children in the intervention group will show fewer escalations of negative affect and more intense shared positive moments with their parents than those in the control group. These effects are expected to be most pronounced in children who show higher baseline emotional sensitivity, operationalized as greater moment-to-moment fluctuations in negative affect prior to the intervention.

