### Power analysis

At the between-person level, an a priori G*Power analysis [27] indicated that 64 participants per group are required to detect a medium effect size (Cohen’s *d* = 0.5), and 26 per group for a large effect size (*d* = 0.8), assuming α = 0.05 and statistical power of 0.80. Previous studies of the IY Dinosaur Child Program have reported effect sizes between 0.70 and 0.81 for improvements in social competence [19], supporting the planned sample size of 120 to allow for potential attrition.

To evaluate intervention effects on intra-individual and dyadic dynamics via daily diaries, simulation-based power calculations were performed. These simulations examined time by condition (intervention vs. control) interactions in multilevel models, with rolling-window correlations nested within participants/families [28]. With 140 time points per child/ family (i.e., 7 days * 20 weeks), statistical power is expected to exceed 80% for detecting small interaction effects (β = 0.005).

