#### Parent-reported outcomes.

***Parenting behavior (Explanatory outcome; RQ1).*** Parenting practices will be measured using the Parenting Practices Interview (PPI) [38]. The PPI includes 73 items rated on a 6-point Likert scale (1 = “never” to 6 = “always”) and covers domains such as positive involvement, inconsistent discipline, and harshness. A sample item is: “When your child misbehaves, how often do you give up trying to discipline him/her?”. Subscale scores will be used to explore potential changes in parenting behavior. Although parents are not enrolled in a formal parenting program, those whose children receive the Dinosaur intervention are indirectly exposed to parenting principles from the IY program. Through weekly letters, reading assignments, and homework exercises derived from the parent book used in the IY parent training, caregivers are encouraged to apply positive parenting strategies at home. The PPI was specifically developed to assess parenting behaviors targeted by the IY parent intervention

***Child externalizing behavior (Primary outcome; RQ1).*** The Child Behavior Checklist (CBCL) will be used to assess children’s behavioral and emotional problems from the parent’s perspective [39]. The CBCL includes 113 items rated on a 3-point scale (0 = “not true”, 1 = “somewhat true”, 2 = “very true”). The Externalizing Problems composite will serve as the primary indicator of behavioral change. To complement this, the Eyberg Child Behavior Inventory (ECBI) will be administered [40]. The ECBI consists of 36 items (e.g., “Refuses to go to bed”) rated for both frequency and problem severity.

***Child social behavior (Primary outcome; RQ1).*** Social competence will be measured using the Social Competence Scale – Parent version (P-COMP) [41]. This 12-item scale uses a 5-point Likert format (1 = “not at all” to 5 = “very well”) to evaluate skills like cooperation, self-control, and empathy. A sample item is: “How well does your child get along with other children?”.

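### Holm's step-down procedure would give the Hypothesis 1 tests the same family-wise error control as the planned Bonferroni thresholds, with power never lower and sometimes clearly higher

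*Protocol article*

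**What the plan says.** In the protocol article, the section on Hypothesis 1 under Statistical analysis plans one latent change score model per primary outcome domain, with condition as predictor of change. It names four domains: "child externalizing behavior, social competence, emotional understanding, and cognitive functioning". It adds: "Outcomes will be analyzed separately for parent-reported, teacher-reported, and child-assessed measures". On multiplicity it says: "Bonferroni-adjusted significance thresholds will be applied to control for multiple comparisons across outcome domains". It gives no divisor and mentions no step-down version.

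The outcome sections label nine measures as primary:
- Parent: CBCL Externalizing, P-COMP, BRIEF-2, CCC-2.
- Teacher: TRF Externalizing, T-COMP, BRIEF-2.
- Child: the two Wally tests.

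The ECBI stands under the primary externalizing heading, but only as an addition to the CBCL ("To complement this, the Eyberg Child Behavior Inventory (ECBI) will be administered"). Counting it would make ten or eleven tests.

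Hypothesis 1 predicts benefit across several domains at once, including "significantly greater reductions in externalizing behavior than children in the control group". The Power analysis section works at an unadjusted level, "assuming α = 0.05 and statistical power of 0.80".

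**The concern.** Bonferroni holds every p-value to α/m. Holm compares the ordered p-values with α/m, α/(m−1), …, α and stops at the first failure. Its first threshold is Bonferroni's and every later one is looser, so it cannot reject less. The family-wise guarantee is the same and needs no assumption about how the outcomes are correlated.

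The choice matters more here than in a trial with one primary outcome. Many outcomes share 120 children, results will be read outcome by outcome, and the hypothesis expects several outcomes to move together, which is the pattern in which step-down testing helps most. What is at stake is that some real effects on single outcomes would be reported as non-significant although an equally strict procedure would have declared them.

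**Working it through.** **1. The plan's own figures.** The Power analysis section states that "64 participants per group are required to detect a medium effect size" (d = 0.5), and "26 per group for a large effect size" (d = 0.8). A two-sided two-sample t-test (noncentral t) with α = 0.05 and power 0.80 gives 63.77, so 64, and 25.52, so 26. Both reproduce. The stated sizes are therefore two-sided and carry no multiplicity adjustment.

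**2. Bonferroni power per outcome, 60 per arm.** The noncentrality is d·√(n/2). At d = 0.5 this is 0.5 × √30 = 2.74, with 118 degrees of freedom.
- α = 0.05: 77.5%
- α = 0.05/4 = 0.0125: 58.1%
- α = 0.05/9 = 0.0056: 46.9%

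**3. Why Holm is valid and never weaker.** Let m₀ of the m null hypotheses be true. When Holm first rejects a true null, at least m₀ hypotheses are still untested, so that p-value is at most α/m₀. By Bonferroni's inequality the chance of this is at most m₀ × α/m₀ = α. For m = 9 the thresholds run 0.05/9, 0.05/8, …, 0.05/1. For m = 4 they are 0.0125, 0.0167, 0.025 and 0.05. The smallest is the Bonferroni threshold, so every Bonferroni rejection is retained.

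**4. Size of the gain.** Simulated equicorrelated two-sided t-statistics, 60 per arm, family-wise α = 0.05, power averaged over the truly affected outcomes. The correlation, the number of affected outcomes and d are assumptions, because the article does not give them. Single pairs of figures are at correlation 0.3. Ranges of gain cover correlations 0 to 0.5.

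| Tests | Truly affected | d | Bonferroni → Holm | Gain, points |
|---|---|---|---|---|
| 9 | 9 | 0.5 | 46.6% → 57.4% | 10.8 (10.5 to 10.9) |
| 9 | 9 | 0.6 | 67.6% → 80.4% | 12.8 (11.7 to 15.0) |
| 9 | 9 | 0.7 | 84.1% → 93.8% | 9.7 (8.6 to 11.1) |
| 9 | 9 | 0.8 | 93.8% → 98–99% | 4.4 to 5.3 |
| 9 | 9 | 0.3 | – | 1.0 to 2.7 |
| 9 | 6 | 0.5–0.7 | – | 4.3 to 6.4 |
| 9 | 5 | 0.5 | 46.9% → 50.5% | 3.6 |
| 9 | 5 | 0.7 | – | about 3.5 |
| 9 | 3 | 0.5–0.7 | – | 1.5 to 2.1 |
| 9 | 1 | 0.5–0.7 | – | 0.1 or less |
| 4 | 4 | 0.5 | – | 9 to 11 |
| 4 | 4 | 0.7 | – | 5 to 6 |
| 4 | 2 | – | – | 1.4 to 2.5 |

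**5. At least one true rejection.** With all nine affected at d = 0.5 and correlation 0.3 the chance is 94.7% under both procedures, because the first step is identical. With five of nine affected it is 87.8% under both.

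**6. Error among the unaffected outcomes.** With five of nine affected at d = 0.5, the chance of any false rejection among the other four is 2.2% under Bonferroni and 3.2% under Holm. At d = 0.7 it is 2.1% and 4.0%. Holm uses more of the 5% allowance and stays within it.

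**7. Attrition.** The article gives no dropout rate. Assuming 15% (51 per arm) with all nine affected, the gain is 7.8 to 9.4 points at d = 0.5, 10.8 to 14.1 at d = 0.7 and 7.1 to 9.0 at d = 0.8.

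**The case against.** Bonferroni is valid, prespecified and conservative. Nothing in the article is wrong or contradictory because of it, and a fuller analysis plan could name a step-down version. A fixed threshold is easy to explain and has matching simultaneous intervals. All of this stands, and it is why the point is an improvement and not a defect. It does not remove the point, because the article itself commits to Bonferroni thresholds and announces no simultaneous intervals that would be lost.

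Three stronger readings are tempting, and the documents do not support them.
- **A fixed loss of some 10 points on every primary outcome.** That is the best case. It needs all nine outcomes to respond at d of about 0.5 to 0.7. Hypothesis 1 predicts broad benefit, but a hypothesis does not establish it. The prior effects that the article cites, 0.70 to 0.81, concern social competence only.
- **A family of exactly nine.** The article adjusts across domains and names four, so nine is one reading. The advantage of Holm holds for either count, but its size differs.
- **Holm as a remedy for a sample size planned at unadjusted α.** At d = 0.5 and nine tests, power falls from 77.5% to 46.9%, and Holm restores at most 57% to 58%. The unadjusted sample size and the unstated family are separate matters.

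The simulation also uses two-group t-statistics, whereas the plan is latent change score models with a pretest. The absolute powers are therefore illustrative. The ordering of the two procedures does not depend on the model.

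**Conclusion.** The point holds as a low-cost improvement. At the same family-wise error, Holm is at least as powerful as the planned thresholds for any family size and any correlation. With nine tests, 60 per arm and an assumed correlation of 0.3, the mean gain per affected outcome runs from near zero (one outcome responds), through about 2 to 4 points (three to five respond), to about 10 to 13 points (all respond at d = 0.5 to 0.7), and back to about 5 points if all respond at d = 0.8, where Bonferroni already has high power. With four tests at d = 0.5 it is about 10 points if all respond and about 2 if two do. The gain is an average over outcomes, and the trial's chance of at least one true finding barely moves. Which case applies cannot be known from the article.

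**What to change.** Replace the multiplicity sentence in the Hypothesis 1 section with:

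> *Holm's step-down procedure at two-sided family-wise alpha 0.05 will be applied across the primary outcome tests (the same family as planned for the Bonferroni adjustment); Holm-adjusted p-values will be reported, and confidence intervals will be labelled as unadjusted for multiplicity.*

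Make the change before outcome data are seen. List the tests in the family at the same time, including whether the ECBI, language and problem-solving measures belong to it, since either procedure needs that list.

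The cost is one sentence and one line of code, with no extra participants or procedures. The real drawback is in reporting: no simple simultaneous intervals correspond to the step-down decisions, so an unadjusted 95% interval may exclude zero beside a non-significant adjusted test. The labelling of the intervals is there to prevent misreading. If simultaneous intervals matter more to the investigators than the extra power, keeping Bonferroni is defensible, and the article should then say so.

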#### Hypothesis 2: Daily variability and behavior problems (ILD-based).

To examine whether the intervention reduces children’s daily emotional variability and behavior problems, multilevel time-series analyses will be conducted on daily parent–child diary data. Daily reports will include ratings of negative affect (e.g., irritability, sadness) and behavior problems (e.g., defiance, tantrums). Repeated observations will be modeled as nested within individuals to capture both group-level trends and within-person variability over time. Fixed effects for time, group, and their interaction will be included to test for differential change trajectories across conditions. In addition, moving window techniques will be employed to capture changes in intra-individual fluctuations and identify evolving temporal patterns of variability throughout the intervention period.

#### Hypothesis 3: Parent–child dynamics (dyadic ILD-based).

To evaluate whether the intervention enhances the emotional quality of daily parent–child interactions, multilevel time-series analyses will be applied to dyadic daily diary data. These models will examine daily reports of shared positive affect and emotional escalation during conflict, with repeated measures nested within families. Time-by-condition interaction terms will be used to assess whether trajectories of affective dynamics differ between the intervention and control groups. Moving window techniques will be used to derive fine-grained temporal indicators of affective synchrony and escalation, allowing for a dynamic examination of how relational processes evolve across the intervention period. This analytic approach offers a detailed understanding of whether the intervention promotes more stable and positive emotional exchanges between parents and children.

## Discussion

Although behavioral interventions such as the IY Dinosaur Program have demonstrated positive effects in supporting young children with conduct problems, substantial heterogeneity in outcomes remains [19,21,24,33]. This study protocol addresses the critical question of what works, for whom, and what are mechanisms of change? By integrating an RCT with a high-frequent ILD design, the Dino Study introduces a novel approach that allows for the examination of both average treatment effects and individual variability in real-life settings. A key innovation of this protocol lies in its combination of group-level standardized assessments and fine-grained, real-time data collection, as well as its comprehensive assessment of outcomes across emotional, behavioral, and cognitive domains. Most intervention studies rely on retrospective reports and pre–post designs, which obscure intra-individual dynamics and parent–child processes that unfold over time [7,8].

ILD collection enables the daily tracking of behavioral and emotional functioning, offering a dynamic, ecologically valid understanding of how children and families respond to structured interventions. Diary and EMA methods reduce retrospective bias and allow for the detection of within-person change processes—such as immediate responses to intervention—that traditional assessments may overlook [52]. This approach provides insight not only into whether a program works, but also into how change unfolds, for whom it is most effective, and under which contextual or emotional conditions. The study is grounded in the Environmental Sensitivity Framework [13], which posits that children differ in their responsiveness to environmental input. By examining moderators such as temperament, executive functioning, and affective variability, the study explores the potential for differential responsiveness to supportive interventions. For example, children who show higher daily emotional reactivity at baseline may be particularly receptive to structured, consistent feedback.

Another important contribution of this study is its focus on affective parent–child dynamics as both an outcome and potential mechanism of change. Rather than limiting evaluation to child behavior alone, daily surveying will provide insights into shared emotional experiences and daily escalation or co-regulation patterns. This level of resolution allows researchers to move beyond the “omnibus effect” typically reported in large-scale RCTs and begin unpacking the micro-level processes that may underlie successful behavior change. At the same time, the study acknowledges the inherent complexity of such data: the intervention is a multi-component program, and causal specificity regarding which elements are most effective may remain difficult to determine.

The waitlist control design allows for strong internal comparisons, but it does not isolate non-specific intervention effects such as increased attention or structure. Furthermore, although the ILD approach is developmentally adapted and only administered once daily, the potential burden on families may still affect compliance and data quality. These limitations are offset, however, by the study’s strengths: the use of certified trainers, implementation in both clinical and preventive settings, and integration of multi-informant data sources, including parent, teacher, and child assessments.

Ultimately, the Dino Study contributes to the emerging movement toward precision prevention in child mental health care. By capturing day-to-day changes and individual differences in responsiveness, this study may help identify subgroups of children for whom structured interventions are especially effective. In doing so, it moves the field closer to personalized, data-informed approaches that respect the complexity of child development and the diversity of family contexts.

### Trial registration

The protocol of this study is registered at ClinicalTrials.gov with identification number NCT07051642 on July 9^th^, 2025. Protocol version 1, date 09.07.2025. The first participant has not yet been recruited. Additional details about the trial registration are presented Table 1.

**Table 1 pone.0330597.t001:** Overview of measurements.

Data category	Information
Primary registry and trial identifying number	ClinicalTrials.gov
	NCT07051642
Date of registration in primary registry	July, 9th, 2025
Secondary identifying numbers	TSB_RP2172
Contact for public queries	[name] e-mail: [contact]
Contact for scientific queries	[name] e-mail: [contact]
	Tilburg University, Tilburg, The Netherlands
Scientific title	The Dino Study: Rationale and study protocol for a randomized controlled trial evaluating the Incredible Years Dinosaur Program with daily assessments
Countries of recruitment	The Netherlands
Health condition(s) or problem (s) studied	Behavior problems in children, parent-child relations, oppositional behavior, executive functioning, and social and language skills
Intervention(s)	Active comparator: Incredible Years Dinosaur Program
	Control group: Waitlist control condition
Key inclusion and exclusion criteria	Ages eligible for study: child, adult, older adult
	Sexes eligible for study: both
	Accepts healthy volunteers: yes
	Inclusion criteria: Dutch-speaking children aged 4–8 years, at least one Dutch-speaking parent willing and able to participate in the study
	Exclusion criteria: intellectual disability in the child (IQ < 70), child lives primarily in a different household during weekdays, parent or child does not have sufficient Dutch language proficiency
Study type	Interventional
	Allocation: randomized, 1:1 assignment
	Masking: single (outcome assessor)
	Primary purpose: treatment
	Phase: not applicable
Estimated study start date	September 2025
Estimated primary completion date	April 2026
Target sample size	120
Recruitment status	Not yet recruiting
Primary outcome(s)	Change in social competence (parent and teacher reports) Change in externalizing behavior (parent and teacher reports) Change in executive functioning (parent and teacher reports) Change in language and communication skills (parent reports) Change in child-assessed emotion understanding and problem solving
Secondary outcome(s)	Daily dynamic emotional processes (ILD-based)
	Daily behavioral processes within families (Dyadic ILD-based)
